### 3 Study objectives and endpoints

#### 3.1 Primary objective

The primary objective of this study is to assess the effect of anakinra in addition to standard treatment on the need for mechanical ventilation in patients with severe COVID-19 and CSS pneumonia.

##### 3.1.1 Primary endpoint

Treatment success, defined as number of patients not requiring mechanical ventilation by Day 15.

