##### 3.2.1 Secondary endpoints supporting the secondary objective

- Total mortality rate (day 28)
- Mortality 48 hours, 7 days, in ICU and hospital
- Viral clearance / viral shedding
- Frequency and severity of AEs:
  - Treatment-emergent severe fatal and life-threatening serious adverse events (SAEs).
  - Adverse events leading to premature discontinuation of study treatment.
  - Anaphylactic/anaphylactoid reactions.

- 
- Anakinra treatment group: Severe neutropenia.
  - Treatment-emergent laboratory abnormalities.

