#### 4.3.2 Exclusion criteria

The presence of any of the following will exclude a patient from inclusion in the study:

- Need for oro-tracheal intubation and/or invasive mechanical ventilation at the start of the study.
- AST/ALT with values greater than 5 times normal levels.
- Neutrophils < 1.500 cell/mmc.
- Platelets < 50.000 cell/mmc.
- Sepsis or pneumonia documented by other pathogens than SARS-CoV-2.
- Existence of any life-threatening comorbidity or any other medical condition that, in the investigator's opinion, makes the patient unsuitable for inclusion.
- Inability to obtain informed consent.
- Positivity for HBV or HCV.
- Patient with active tuberculosis (It is at the discretion of the researcher to perform the tuberculin test on the patient in the screening period if it is considered a risk population and on patients with active tuberculosis manifestations).
- Pregnancy.
- Use of other previous or concomitant biological treatments. Patients in concomitant treatment with other biologicals that may interfere will be excluded: tocilizumab, canakinumab, TNFalfa inhibitors, JAKinibs
- Severe renal dysfunction (estimated glomerular filtration rate  $\leq 30$  ml / min / 1.73 m^2) or receive continuous renal replacement therapy, hemodialysis or peritoneal dialysis.
- Uncontrolled hypertension (sitting systolic blood pressure > 180 mmHg or diastolic blood pressure > 110 mmHg).
- Administration of plasma from convalescent patients who have recovered from SARS-CoV-2 infection.
- History of hypersensitivity or allergy to any component of the study drug.
- Enrollment in another concurrent intervention clinical trial, or intake of an investigational medication within three months or 5 half-lives prior to inclusion in this study, if deemed to interfere with the objectives of this study as assessed by the investigator.

- Predictable inability to cooperate with given instructions or study procedures.

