#### 4.3.3 Withdrawal of patients from treatment or study

##### 4.3.3.1 *Withdrawal from treatment*

A patient should be withdrawn from the study treatment if, in the opinion of the Investigator, it is medically necessary, or if it is the wish of the patient.

When a patient is withdrawn, the date of last IMP (investigational medicinal products) administration and the date and reason for treatment withdrawal should be clearly described in the relevant sections of the CRF. If a patient is removed from treatment because of an AE, the reason for treatment withdrawal should always be stated as 'adverse event' irrespective of whether this was the investigator's or the patient's decision.

If a patient withdraws due to worsening of disease, patient should be treated as a non-responder. In these case, the patient will be able to receive treatments that are protocolized at their hospital. The patient could be treated with pulses of steroids, intravenous immunoglobulins, betainterferon and other biologic or immunosuppressants agents such as cyclosporin, tacrolimus, baricitinib, tocilizumab, sarilumab, ruxolitinib...

The patient will continue to participate in the study without taking study treatment.

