#### 4.5.3 Efficacy assessments

##### *4.5.3.1 Pulmonary function (primary efficacy assessment)*

The date and time of the requirement for mechanical ventilation will be assessed at Visits 1 to 4, and recorded in the CRF.

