### 6.3.3 Analysis related to primary objective

#### *6.3.3.1 Primary endpoint*

##### Treatment success

The main outcome variable is the percentage of patients requiring mechanical ventilation at 15 days after the start of treatment. The comparison of these proportions would be done by chi-square test, with significance level 0.05 and presentation in the form of absolute risk

reduction, relative risk reduction and number needed to treat, with their respective 95% confidence intervals.

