#### 6.3.4 Analysis related to secondary objective

##### *6.3.4.1 Mechanical ventilation at day 28.*

The percentage of patients requiring mechanical ventilation at 28 days after the start of treatment. The comparison of these proportions would be done by chi-square test, with significance level 0.05 and presentation in the form of absolute risk reduction, relative risk reduction and number needed to treat, with their respective 95% confidence intervals.

---

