#### 6.3.8 Handling of missing data

There will be no computation of missing data.

---

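### The primary endpoint leaves death unassigned, so a patient who dies by Day 15 without ventilation, and without prior withdrawal for worsening, counts as a treatment success

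*Protocol*

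**What the plan says.** Section 3.1.1 of the protocol defines the primary endpoint: "Treatment success, defined as number of patients not requiring mechanical ventilation by Day 15". The analysis section, 6.3.3.1, puts it this way: "The main outcome variable is the percentage of patients requiring mechanical ventilation at 15 days after the start of treatment". Section 6.3.4.1 uses the same form for the later endpoint: "The percentage of patients requiring mechanical ventilation at 28 days after the start of treatment". None of the three mentions death or extubation.

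Other parts of the protocol bear on the point:

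- **Non-responder rule** (4.3.3.1, repeated in 4.4.9): "If a patient withdraws due to worsening of disease, patient should be treated as a non-responder". Sections 3.1.1 and 6.3.3.1 do not refer to it.
- **Missing data** (6.3.8): "There will be no computation of missing data".
- **Mortality** is a separate secondary objective (3.2, 3.2.1, 6.3.4.2, 6.3.4.3).
- **Data for the endpoint** (4.5.3.1): "The date and time of the requirement for mechanical ventilation will be assessed at Visits 1 to 4, and recorded in the CRF".
- **Ventilation at entry** (4.3.2) excludes: "Need for oro-tracheal intubation and/or invasive mechanical ventilation at the start of the study". Here the type of ventilation is named; in the endpoint it is not.
- **Blinding** (4.4.6): none.

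**The concern.** Death before Day 15 prevents later ventilation. If the endpoint counts only ventilation, a patient who deteriorates and dies without it falls on the favourable side of the comparison. Patients are up to 80 years old with severe pneumonia, and mortality is the secondary objective, so such deaths are foreseeable. Staff know the treatment arm, so the path from deterioration to ventilation, or to death without it, could differ between arms for reasons other than drug effect. A difference in unventilated deaths would then move the primary result in the wrong direction.

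The wording of the analysis adds a second uncertainty. *By Day 15* counts anyone ventilated up to then. *At 15 days* can also mean ventilated on that day. On the second reading, a patient ventilated on Day 3 and extubated or dead on Day 12 is not a failure. Two analysts could derive different primary results from the same data.

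Third, a patient may enter on non-invasive support, because only invasive ventilation is excluded. Whether such support counts as the endpoint event is not stated.

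**Working it through.** **Who counts as what, from the text**

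| Patient by Day 15 | Section 3.1.1 | Section 6.3.3.1 read as status on Day 15 |
|---|---|---|
| Ventilated, still ventilated | failure | failure |
| Ventilated, then extubated or dead | failure | not a failure |
| Withdrawn for worsening | non-responder by 4.3.3.1, if that rule is applied | same |
| Died unventilated, no prior withdrawal | success | success |

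**Inputs from section 6.1.** Success is 88% on standard of care and 92% on anakinra, so ventilation is 12% and 8%. There are 90 patients per arm with a 10% loss, so 90 × 0.9 = 81 evaluable. Type I error is 0.05 (sidedness not stated) and power is 75%.

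**The plan's own figure.** The usual formula is n = [z(1−α/2)·√(2p̄q̄) + z(1−β)·√(p₁q₁ + p₂q₂)]² / (p₂ − p₁)². With two-sided 0.05 it gives [1.960·√0.18 + 0.674·√0.1792]² / 0.04² = 780 per arm, or 780/0.9 = 867 after loss. One-sided it gives 605, or 673 after loss. The stated 90 is not reproduced. That is a separate defect, and nothing below depends on it.

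**Size of the planned effect in patients.**
- Expected ventilated per 90: 0.12 × 90 = 10.8 and 0.08 × 90 = 7.2, a gap of 3.6.
- Per 81: 0.04 × 81 = 3.24.

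**Unventilated deaths.** The protocol gives no rate, so I assume 0% to 10% per arm. Composite success (alive and never ventilated) is the success rate as written minus the unventilated death rate.

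| Assumed unventilated death, standard of care / anakinra | Endpoint as written | Alive and unventilated | Difference |
|---|---|---|---|
| 0% / 0% | 88 vs 92% | 88 vs 92% | 4 points |
| 2% / 2% | 88 vs 92% | 86 vs 90% | 4 |
| 5% / 5% | 88 vs 92% | 83 vs 87% | 4 |
| 10% / 10% | 88 vs 92% | 78 vs 82% | 4 |
| 2% / 6% | 88 vs 92% | 86 vs 86% | 0 |
| 5% / 9% | 88 vs 92% | 83 vs 83% | 0 |
| 5% / 10% | 88 vs 92% | 83 vs 82% | −1 |
| 5% / 3% | 88 vs 92% | 83 vs 89% | 6 |

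Only an imbalance changes the difference, and it can act either way. An imbalance of 4 points is 3.6 deaths per 90.

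**Status reading.** Let f be the share of ventilated patients extubated or dead before Day 15, assumed equal in both arms. The counted failure rate is the ventilation rate × (1 − f).

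| f (assumed) | Counted failures per 90 | Difference |
|---|---|---|
| 0% | 10.8 vs 7.2 | 4.0 points |
| 20% | 8.6 vs 5.8 | 3.2 |
| 40% | 6.5 vs 4.3 | 2.4 |
| 60% | 4.3 vs 2.9 | 1.6 |

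**The case against.** **The wording is loose, not contradictory.** Section 6.3.3.1 stands under the label of treatment success, the term that 3.1.1 defines cumulatively. Sections 4.1 and 4.5.1.5 speak of evaluating the endpoint at Day 15, which suits a cumulative count taken then. Section 4.5.3.1 records the date and time of the requirement, 6.3.3.2 analyses time to ventilation, and 6.1 relies on patients who had required it. This stands. A reader might infer that the protocol contradicts itself here, but it shows only an ambiguity. It follows that a benefit from faster death on the ventilator arises only under the less likely reading.

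**Requiring is not receiving.** The objective in 3.1 is the need for ventilation, so a patient who needed it and did not get it might already be a failure. This is possible, but the protocol does not define need apart from ventilation, and it would not cover a death with no recorded need.

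**Deterioration is partly handled.** The non-responder rule catches patients withdrawn for worsening, and the mortality endpoints would show excess deaths beside the primary result. Both are true. Neither assigns a death without prior withdrawal, and a secondary endpoint does not repair the primary test.

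**Intubation limited by ICU capacity.** A reader might infer this as a known source of bias. Sections 2.1 and 2.2 speak only of preserving ICU access. They do not say that decisions to intubate were constrained.

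**Left to an analysis plan.** Details could be, but the protocol itself fixes the primary endpoint and its analysis variable, and both omit death.

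**Conclusion.** The point holds. The primary endpoint and its analysis count ventilation only, and a death by Day 15 without ventilation or prior withdrawal for worsening is a success as written. A net between-arm imbalance of about 4 such deaths (3.6 per 90, 3.2 per 81) would offset the whole planned effect. It would be too strong to say that any 3 or 4 such deaths create or erase the effect, because equal numbers in both arms leave the 4-point difference as it is. The rates in the tables are assumptions, and the documents do not show which way any bias would run.

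The timing wording and the type of ventilation are unresolved ambiguities to be closed at the same time. That a patient on non-invasive support would be a failure on Day 1 is likewise only one possible reading, because the protocol does not say whether such support counts.

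**What to change.** 1. In 3.1.1 and 6.3.3.1, define primary failure as invasive mechanical ventilation or death from any cause at any time from randomisation through Day 15, counted even if the patient is later extubated.
2. Write *by Day 15* in 6.3.3.1 and *by Day 28* in 6.3.4.1.
3. Report ventilation alone and death alone as components of the composite.

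**Cost for Day 15:** mainly wording. Ventilation dates are recorded at Visits 1 to 4 (4.5.3.1), fatal events are reported (4.5.4.3), and survival is collected at follow-up (4.5.3.7, Table 3).

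**Cost for section 6.1:** the assumed success rates must be restated for the composite. If the 4-point difference is kept and unventilated deaths are equal at an assumed 2%, 5% or 10%, the formula above (two-sided 0.05, 75% power) gives 916, 1106 or 1388 per arm before loss, against 780 with none.

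**Cost for Day 28:** more than wording. Ventilation is assessed only to Visit 4, so the date of any ventilation between Day 15 and Day 28 must be recorded at the existing Visit 5 contact.

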##### 3.1.2 Secondary endpoints supporting the primary objective

- Number of patients not requiring mechanical ventilation (day 28).
- Time to mechanical ventilation (days)
- Time to oxygen saturation normalization
- Stay in ICU and hospitalization (days)

#### 3.2 Secondary objective

The secondary objective of this study is to assess the effect of anakinra in addition to standard treatment on mortality in patients with severe COVID-19 and CSS pneumonia.

##### 3.2.1 Secondary endpoints supporting the secondary objective

- Total mortality rate (day 28)
- Mortality 48 hours, 7 days, in ICU and hospital
- Viral clearance / viral shedding
- Frequency and severity of AEs:
  - Treatment-emergent severe fatal and life-threatening serious adverse events (SAEs).
  - Adverse events leading to premature discontinuation of study treatment.
  - Anaphylactic/anaphylactoid reactions.

- 
- Anakinra treatment group: Severe neutropenia.
  - Treatment-emergent laboratory abnormalities.

### 3.3 Exploratory objective

To assess the effect of anakinra on IL-6, ferritin, and selected biomarkers relevant for hyperinflammation, MAS and cytokine storm change from baseline.

#### 3.3.1 Exploratory endpoints

- Change (improvement) in IL-6, ferritin, D-dimer, TGs, lymphopenia, CRP, ESR, LDH.
- Time to defervescence (fever end)

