## 4 Investigational plan

### 4.1 Overall study design and plan

This is a randomized, open-label, parallel group, 2-arm multicenter study to investigate the efficacy and safety of anakinra in reducing hyper-inflammation and respiratory distress in adult patients with severe COVID-19 and CSS pneumonia.

The study consists of screening, a 2-week treatment period and a 2-week follow-up period.

The 2-week treatment period is open, and the patients will be randomized to treatment with anakinra + standard of care or standard of care alone in a 1:1 ratio.

Anakinra will be administered as 4-times daily i.v. infusions for a maximum of 15 days (Days 1 to 15), according to the patient health status and expert clinical opinion. The primary endpoint will be evaluated at Day 15.

According to hospital internal protocol, if the patient improves enough to recommend his/her discharge before the 15th day of the study, the patient will be able to continue receiving the medication at home by s.c. administration (100mg/6 hours). In any case, follow-up visits by telephone or in person will be made, depending on where the patient is, until the end of the study.

The study duration for an individual patient will not exceed 4 weeks. The end of the study is defined as last patient last follow-up visit/phone call.

Figure 1:

[figure not shown]

The study design has a total sample size of 180 patients and consists of two stages. At the end of the treatment stage, the success rates are compared between each arm: anakinra + standard of care treatment vs standard of care alone.

A data review committee composed of experts in internal medicine will be involved in the study oversight and interpretation of the study results.

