## 4.2 Discussion of study design, including the choice of control groups

## 4.3 Selection of study population

### 4.3.1 Inclusion criteria

A patient must fulfill the following criteria in order to be included in the study:

- Age 18-80 years.
- Severe pneumonia COVID-19 defined as:
  - Nasopharyngeal smear with RCP positive for SARS-CoV-2
  - X-Rays (or other technique) pulmonary infiltrates compatible with pneumonia.
  - 1 or more of the following criteria:
    - Ambient air oxygen saturation  $\leq 94\%$  measured with a pulse oximeter.
    - Pa:FiO2 (partial pressure O2/fraction of inspired O2)  $\leq 300$ .
    - Sa:FiO2 (O2 saturation measured with pulse oximeter/ fraction of inspired O2)  $\leq 350$ .
- High suspicion of CSS that could resemble MAS-like: represented by IL-6 values  $> 40$  pg/mL and/or ferritin  $> 500$  ug/L and/or PCR  $> 30$  mg/L (rationale:  $\geq 5$  upper normal limit) and/or LDH  $> 300$  UI/L. We have chosen these parameters because they are implemented in all the participating hospitals, they are a reflection of the cytokine storm and they have also been significant in terms of predicting mortality in patients with COVID-19 (9).
- Written informed consent. The protocol will be explained to the patient in front of a nurse who will act as a legal witness by signing the document on behalf of the patient.

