### 4.5 Efficacy and safety assessments

#### 4.5.1 Study schedule

##### 4.5.1.1 Schedule of events

Measurements will be done during screening (before Day 1), at Day 1, Day 4, Day 7, and Day 15 and Day 28.

Table 3: Clinical and laboratory parameters to be collected

| ASSESSMENT             | SCREENING        | TREATMENT PERIOD |         |         |                  | Follow-up         |
|------------------------|------------------|------------------|---------|---------|------------------|-------------------|
|                        | Prior to Visit 1 | Visit 1          | Visit 2 | Visit 3 | Visit 4          | Visit 5/TC        |
|                        |                  | Day 1 (Baseline) | Day 4   | Day 7   | Day 15 (± 2 day) | Day 28 (± 2 days) |
| Informed consent       | X                |                  |         |         |                  |                   |
| Eligibility criteria   | X                | X                |         |         |                  |                   |
| Patient information    | X                |                  |         |         |                  |                   |
| Physical examination   | X                |                  |         |         |                  |                   |
| Vital signs assessment | X                | X                | X       | X       | X                |                   |
| EKG assessment         | X                |                  |         |         | X                |                   |
| Chest X-Ray            | X                |                  |         |         | X                |                   |

|                                                |   |     |   |   |   |   |
|------------------------------------------------|---|-----|---|---|---|---|
| Laboratory assessments (local)                 | X | X   | X | X | X |   |
| Urine pregnancy test                           | X |     |   |   | X |   |
| Randomization                                  |   | X   |   |   |   |   |
| IMP administration                             |   | X X |   |   |   |   |
| Concomitant medication incl background therapy |   | X   | X | X | X |   |
| Pulmonary function                             |   | X   | X | X | X |   |
| PaO 2 /FiO 2             | X |     |   |   | X |   |
| Resting SpO 2 (3 times per day)     |   | X   | X | X | X |   |
| Oxygen supplementation                         |   | X   | X | X | X | X |

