#### *4.5.1.4 Visits 2 to 3 (Days 4 and 7)*

Please refer to Table 3 for the clinical and laboratory parameters to be collected during these visits. For study drug administration schedule, see Section 4.4.1.

Effort should be made to adhere to the schedule of assessment. However, a window of  $\pm 1$  day will be allowed for all assessments scheduled. This does not include IMP administration.

During the treatment period, clinical and laboratory assessments and procedures should preferably be performed before IMP administration.

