##### *4.5.3.3 SpO2*

Resting peripheral capillary oxygen saturation (SpO2) will be measured 3 times per day by pulse oxymetry at Visits 1 to 4 and recorded in the CRF. Saturation normalization will be measured, both as an absolute value and as a relative value with respect to the baseline situation of income.

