#### *4.5.4.7 Vital signs*

Vital signs (body temperature, blood pressure, heart rate, respiratory rate and oxygen saturation) will be measured at screening, and Days 1, 4, 7 and 15, and recorded in the CRF.

For AE reporting of abnormalities, see Section 4.5.4.3.

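### Time to defervescence cannot be measured to the day, because temperature is recorded only at screening and on Days 1, 4, 7 and 15

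*Protocol*

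**What the plan says.** Protocol 3.3.1 names "Time to defervescence (fever end") among the exploratory endpoints.

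Temperature enters the CRF as a vital sign. Section 4.5.4.7 lists "Vital signs (body temperature, blood pressure, heart rate, respiratory rate and oxygen saturation") and says that these "will be measured at screening, and Days 1, 4, 7 and 15, and recorded in the CRF". Table 3 in 4.5.1.1 agrees. The general schedule there reads "Measurements will be done during screening (before Day 1), at Day 1, Day 4, Day 7, and Day 15 and Day 28", but the vital signs row has no mark at Day 28.

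The visits may move. For Days 4 and 7, section 4.5.1.4 gives a window of one day either side: "day will be allowed for all assessments scheduled". Table 3 and 4.5.1.5 allow two days either side of Day 15.

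Fever is not needed for entry. Section 4.3.1 requires a positive PCR, infiltrates, an oxygenation criterion and a laboratory signal, the last introduced as "High suspicion of CSS that could resemble MAS-like: represented by IL-6 values" and continuing with ferritin, CRP and LDH.

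Other assessments get finer data. SpO2 "will be measured 3 times per day by pulse oxymetry at Visits 1 to 4" (4.5.3.3). Sections 4.5.3.1 and 4.5.3.4 ask for the date and time of the need for mechanical ventilation and of oxygen supplementation. Nothing comparable is asked for fever.

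**The concern.** A time-to-event endpoint needs either the date of the event or readings close enough together to place it. Here the protocol collects neither. Fever that ends between two visits is first seen to have ended at the later visit, so the recorded time reflects the visit calendar as well as the illness. The longest gap, Day 7 to Day 15, makes up more than half of the treatment period. After early discharge even the scheduled reading may be missed by site staff, since "follow-up visits by telephone or in person will be made, depending on where the patient is" (4.1).

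The second difficulty is who contributes. A patient without fever on Day 1 has no fever end to time, yet nothing in 3.3.1 restricts the endpoint to febrile patients.

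At stake is whether a reported median time to defervescence, or a difference in medians, describes patients or visit days. A statistical analysis plan can choose a method, but it cannot recover temperatures that were never collected.

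**Working it through.** The protocol gives no effect size or power for this endpoint, so there is no stated figure to reproduce.

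**Inputs.** Temperature days 1, 4, 7 and 15 (4.5.4.7, Table 3); windows of ±1 day for Days 4 and 7 (4.5.1.4) and ±2 days for Day 15 (Table 3, 4.5.1.5). Rule: fever end is recorded at the first temperature day on or after it.

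**Step 1: gaps.** Nominal: 4 − 1 = 3, 7 − 4 = 3, 15 − 7 = 8 days. With the windows, the last gap runs from 13 − 8 = 5 to 17 − 6 = 11 days.

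**Step 2: pairs of patients one day apart.** There are 14 adjacent-day pairs between Day 1 and Day 15.

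| True days of fever end | Recorded difference | Pairs |
|---|---|---|
| 1 v 2, 4 v 5 | 3 days | 2 |
| 7 v 8 | 8 days | 1 |
| All others | 0 days | 11 |

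No pair is recorded as one day apart. This step needs no distributional assumption.

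**Step 3: recorded medians.** Assume exponential time after Day 1 with median m days. The probability that fever has ended by Day d is 1 − 2^(−(d−1)/m).

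| m (days) | By Day 4 | By Day 7 | Recorded median |
|---|---|---|---|
| 4 | 1 − 2^(−3/4) = 41% | 1 − 2^(−6/4) = 65% | Day 7 |
| 5 | 1 − 2^(−3/5) = 34% | 1 − 2^(−6/5) = 56% | Day 7 |
| 7 | 1 − 2^(−3/7) = 26% | 1 − 2^(−6/7) = 45% | Day 15 |
| 9 | 1 − 2^(−3/9) = 21% | 1 − 2^(−6/9) = 37% | Day 15 |

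True medians of 4 v 5 days, or of 7 v 9, show no difference in recorded medians. True medians of 5 v 7 show 15 − 7 = 8 days.

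**Step 4: average delay.** Worked for m = 2, among patients whose fever ends by Day 15. The shares recorded at Days 4, 7 and 15 are 0.646, 0.229 and 0.117, total 0.992.
- Mean recorded day: (4 × 0.646 + 7 × 0.229 + 15 × 0.117) / 0.992 = 5.99.
- Mean true day: 1 + 2/ln 2 − 14 × 2^(−7) / (1 − 2^(−7)) = 3.77.
- Delay: 5.99 − 3.77 = 2.2 days.

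Simulation of 400,000 times per median, for medians of 2 to 9 days, gives mean delays from 2.2 to 2.8 days. The share of patients whose fever ends in the Day 7 to 15 gap is 2^(−6/m) − 2^(−14/m): 12% for m = 2 and 30% for m = 7.

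**Step 5: effect on the comparison of arms.** Simulated log-rank test, assuming 90 febrile patients per arm, exponential times and no missing data:

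| True medians (days) | Power, daily readings | Power, visit days only |
|---|---|---|
| 2 v 3 | 77% | 72% |
| 3 v 5 | 90% | 88% |
| 5 v 7 | 53% | 50% |
| 7 v 9 | 31% | 30% |

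Type I error is about 5% under both schedules. When every fever end is shifted by one day, about 80–82% of shifts are recorded as 0, 10–15% as 3 days and 5–8% as 8 days. The mean recorded difference stays near 0.9 to 1.0 day.

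**The case against.** The strongest reply is that the endpoint is coarse but not lost. Both arms share the same calendar, so the data are interval-censored times that can be compared fairly. Step 5 bears this out. A reader might infer that the endpoint cannot be measured at all, or that real differences between arms vanish. The documents do not support that: the protocol does not commit to comparing medians, and true medians of 2 v 3 days still put 65% v 50% of patients afebrile by Day 4.

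A reader might also infer that a one-day difference generally turns into eight days. It does so for one pair of individual days in 14, and arm medians jump by eight days only when they lie on either side of Day 7.

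It can be said, too, that visits can capture dates between them, as 4.5.3.1 does for ventilation, and that hospital charts are the source data (7.3). That route is open, but the protocol does not take it for fever.

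Finally, the fever threshold, any rule for sustained absence of fever and the handling of death are commonly left to the statistical analysis plan. Their absence is no finding here. Day 1 temperature is collected, so febrile patients can be identified.

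**Conclusion.** The point holds as a limit on resolution. Time to defervescence is known only to within nominal gaps of 3, 3 and 8 days. Recorded times and medians would sit on visit days and run late by about 2.2 to 2.8 days on average. That delay assumes exponential times from Day 1 and readings on the nominal days; the adjacent-day count (11 of 14 recorded as equal) assumes only the nominal days. The test between arms remains valid, with a power loss of about 1 to 5 points if all 90 patients per arm are febrile and none are missing. Fewer febrile patients would lower power under either schedule. The harm is therefore confined to the estimated times and medians of an exploratory endpoint, and to patients afebrile on Day 1, who have no event to time. This is a cheap improvement and does not threaten the trial's conclusions.

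**What to change.** In 4.5.4.7, ask sites to transcribe the daily maximum temperature from the routine ward chart for each day in hospital. In 3.3.1, limit time to defervescence to patients febrile on Day 1. With daily values, a one-day difference is recorded as one day while the patient is an inpatient; after discharge the data still depend on the scheduled contacts.

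If daily values will not be transcribed, replace the endpoint with the proportion afebrile at Days 4, 7 and 15 among patients febrile on Day 1. The planned schedule supports that.

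The first option costs one CRF line per inpatient day. The second costs nothing to collect but gives up the time scale. Both reduce the analysis set to patients with fever at baseline.
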